### 3.3. Blinding

This will be an unblinded study.

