### 2.4. Training for Evaluation Moments

At the beginning of the study, 6 field workers and 2 nursing technicians will be selected from the study area and trained. The one-week training will incorporate: (1) an introduction to the research questions, goals and study design; (2) basic concepts regarding the diseases studied; (3) methodologies for data collection (structured interviews, anthropometric evaluations, recognition of signs and symptoms of micronutrient deficiency, measurement of temperature); and (4) communication skills and the collection/delivery of information. Additionally, nursing technicians will undergo 3-day training on: (1) the treatment and referral protocol adopted in this study; (2) best practices for drug administration in young children; and (3) the management of domiciliary and health unit treatments. Blood, urine and stool samples will be collected before their processing by experienced CISA resident laboratory technicians. A field work simulation class will be conducted with all personnel involved in this survey at the end of all training sessions.

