### 2.5. Recruitment of Participants

A house-to-house recruitment team will identify the children eligible in each hamlet, explaining the importance of the study both to local authorities and caretakers, delivering stool and urine containers and explaining the best practices for sample collection. This team will recruit up to 45 children per day, and orient them to attend the next evaluation at the hamlet health post. Those evaluations will be carried out in each hamlet until all eligible willing-to-participate families have been notified.

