### 2.6. Baseline Data Collection and Sample Storage

A structured questionnaire is to be administered to mothers or other primary caretakers to collect information on identification, breastfeeding, complementary feeding practices and health care practices, supplementation and vaccination history, WASH and malaria practices. Weight and height, collected using electronic or platform pediatric scales and measuring harness or adult stadiometer, will be used to calculate anthropometric indices for the diagnosis of undernutrition in children and mothers according to WHO standards [45,46]. Peripheral blood will be collected in accordance with WHO good phlebotomy practices [47]. For biochemical analyses, blood will be collected in 1.1ml Z-Gel microvette tubes, centrifuged for the separation of the serum and stored at −20 °C and blood for molecular analysis will be stored in air-dried filter paper until processing. Mothers/caretakers will be instructed to collect a stool sample on the day before evaluation and to collect urine in the morning of evaluation day. Urine samples are to be conserved in formalin (10%) to prevent larvae eclosion.

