### 2.7. Sample Processing

Stool, urine and blood will be analyzed parasitologically. Blood protozoa (*Plasmodium falciparum* and *Plasmodium vivax*) will be determined by the Rapid diagnostic test (*SD BIOLINE* Malaria Ag P.f/P.v (HRP-2/pLDH, Standard Diagnostics, INC, Suwon City, Korea))*,* intestinal helminths (*Ascaris lumbricoides, Trichuris trichiura*, *Hymenolepis nana* and *Strongyloide stercoralis*) determined through fecal smear according to the Katokatz technique, intestinal protozoa (*Giardia lamblia* and *Entamoeba hystolitica/dispar*) evaluated through fecal centrifugal-sedimentation (using Parasitrap® System, Biosepar, Mühldorf, Germany) and urogenital helminth (*Schistosoma haematobium*) determined by urine filtration [48,49]. Biochemical analyses will comprise quantifying hemoglobin directly from peripheral blood (using Hemocue ® Hb 301 System, Angelholm, Sweden), serum ferritin, C-reactive protein and zinc through kits from Quimica Clínica Aplicada (Quimica Clínica Aplicada S.A., Tarragona, Spain) and an automated analyzer (BT1500, Biotecnica Instruments S.p.A, Rome, Italy), serum retinol through high-performance liquid chromatography with a protodiode-array detection, and vitamin B12 and folic acid by chemiluminescence immunoassay (using VITROS® Immunodiagnostic kits, Ortho Clinical Diagnostics, Inc. Bridgend, UK) [50,51,52,53]. Molecular analysis will include DNA extraction (by Chelex method), screening for sickle cell trait and disease (by PCR) and G6PD deficiency (by rtPCR) [54,55]. Malaria diagnosis will take place on site, and stool/urine samples will be analyzed within 24/48 h of collection (depending on the day of the week). The laboratory analyses will be performed by trained technicians and 25% of tests subject to confirmation by experienced laboratory supervisors.

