### 3.2. Randomization

The hamlets will be considered as cluster units. For randomization, the names of the hamlets will be written down on pieces of paper and placed in a bag and then successively removed. The first two papers to be removed will be attributed to the Nutrition arm, the following two to the WASH/Malaria arm and the next pair to the control with this procedure repeated until there are no papers left in the bag. This process will be carried out by the two CISA researchers coordinating the study.

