## 4. Data Collection

### Educational Interventions

Caretakers participating in the intervention arms will have a monitoring file (consisting of six structured questionnaires (one for each monthly visit), applied by the technician to document behavioral alterations at every counselling visit and to record attendance to the community group sessions. Those educational interventions will be intercalated with cross-sectional evaluations. Those moments will have the same design as the baseline assessment, occurring respectively six and twelve months after the beginning of the study.

Data on the primary and secondary outcomes, which will be collected only in the follow up moments, aim at evaluating the impact of interventions. Considering that interventions are expected to influence either health and behavioral aspects, impact indicators are expected to provide information on changes in their frequency, and potential associations. On the other hand, data on the process indicators, which will be collected throughout the study, aim at assisting the evaluation of the quality and success of intervention’s delivery process. Thus, data regarding the provision, utilization and coverage aspects of the delivery process are expected to facilitate attributing the changes in primary and secondary outcomes to the intervention, by demonstrating that the intervention was of sufficient magnitude and occurred in a temporal sequence. Specifically, (1) provision indicators are expected to inform about the quality of provider’s training and performance, and if the requirements for provider’s optimal performance was delivered to them; (2) utilization indicators are expected to inform about the quality of receiver’s sensibilization, their receptivity to interventional activities, acquired knowledge and alterations of inadequate behaviors toward children; and (3) coverage indicators aim at providing information regarding the quality of the interventional activities, such as the adherence to them.

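### The trial is declared unblinded as a whole, although laboratory readers, confirming supervisors and the analyst could be masked cheaply, mainly to protect secondary infection and micronutrient outcomes

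*Protocol article*

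**What the plan says.** Section 3.3 is a single sentence: "This will be an unblinded study". It makes no exception for the laboratory, the quality re-check or the analyst.

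Other sections describe how specimens arise and are read:

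- Section 3.2 allocates by hamlet: "The hamlets will be considered as cluster units".
- Section 2.5 describes work at the hamlet health post: "Those evaluations will be carried out in each hamlet until all eligible willing-to-participate families have been notified". The stated pace is "This team will recruit up to 45 children per day".
- Section 4 repeats this after allocation: "Those moments will have the same design as the baseline assessment, occurring respectively six and twelve months after the beginning of the study".
- Section 2.4 separates the laboratory from the field team: "samples will be collected before their processing by experienced CISA resident laboratory technicians".
- Section 2.7 plans a quality check, with "25% of tests subject to confirmation by experienced laboratory supervisors". It does not say whether the supervisors are masked to arm or to the first reading. Stool and urine are read within 24/48 h.
- Section 2.6 says that blood for biochemistry is "centrifuged for the separation of the serum and stored at" −20 °C.

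Table 2 lists hemoglobin variation and anemia prevalence as primary outcomes. Prevalence, intensity, incidence and reinfection of parasites, and micronutrient deficiencies, are secondary.

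**The concern.** The blanket sentence gives up a protection that the design could keep. A fecal smear or a urine filter is read by eye, and the call on a light infection, or the egg count behind an intensity grade, leaves room for judgement. A reader who knows that a specimen comes from a WASH/malaria hamlet may expect fewer infections. The re-check has the same exposure if the supervisor also knows the arm.

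The second exposure is the order of work. Frozen sera can be assayed in any order, so run-to-run drift can be kept out of the arm comparison by design. If a run happened to hold one arm only, drift and arm could not be separated afterwards. Likewise, if the follow-up calendar were worked arm by arm, season would become part of the arm difference, for hemoglobin too.

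At stake are mainly the infection and micronutrient outcomes. They are meant to show by which pathway each intervention acts.

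**Working it through.** The article states no figure for this point, so there is none to reproduce. The check sets the sections side by side and then sizes the exposure under stated assumptions.

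**Who needs to know the arm?** Section 3.4 assigns the field and nursing technicians to arms and makes them the counsellors. Laboratory technicians are not named there. Table 1 gives diagnosis and treatment in all three arms, so a positive result can go back to the treating staff by study number without the arm. No stated laboratory task needs it.

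**Which outcomes can masking reach?** (methods from Section 2.7, outcomes from Table 2)

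| Outcome | How it is read | Effect of laboratory masking |
|---|---|---|
| Hemoglobin, anemia (primary) | Device, directly on peripheral blood | Little |
| Malaria | Rapid test on site | Little; not read in the laboratory |
| Stool and urine parasites | Microscopy within 24/48 h | Real but partial |
| Ferritin, CRP, zinc, retinol, B12, folate | Instruments | Small for reader expectation; run mixing matters more |

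**Reader expectation.** Assume true prevalence p in both arms and a relative shift r in calling light infections in one arm. False difference = p × r. With p = 12% and r = 10% this is 0.12 × 0.10 = 1.2 percentage points. Half that shift gives 0.6 and double gives 2.4. Both inputs are assumptions.

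**Number of hamlets.** Section 2.1 mentions 15 hamlets with health facilities and keeps only those with daily primary care, so 15 is a ceiling. Section 3.2 draws in pairs in the order nutrition, WASH/malaria, control. Six hamlets give 2/2/2, nine give 4/3/2, twelve give 4/4/4 and fifteen give 6/5/4.

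**Serum runs.** Assume a between-run coefficient of variation (CV) of 5–10% and independent run effects.

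- One run per arm: standard error added to an arm difference = CV × √2 = 7.1–14.1% of the mean, inseparable from the arm.
- One run per hamlet, with a and b hamlets in the two arms: CV × √(1/a + 1/b). At 2 and 2 this is CV × 1 = 5–10%. At 6/5/4 it runs from CV × √(1/6 + 1/5) to CV × √(1/5 + 1/4), that is 3.0–6.7% over the CV range. This is extra between-hamlet noise, not bias.
- All arms in equal share in every run: the run effect cancels.

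The article does not say which of these applies.

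**Visit calendar.** If hamlets are visited one at a time in random order, two arms with a and b hamlets fall in wholly separate parts of a round with probability 2 / C(a+b, a):

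- 6 hamlets: 2/6 = 33%
- 9 hamlets: 2/35 = 6% to 2/10 = 20%, depending on the pair of arms
- 12 hamlets: 2/70 = 3%
- 15 hamlets: 2/462 = 0.4% to 2/126 = 1.6%

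Working arm by arm, the mean visit positions of the first and last arm would differ by 4/5 = 80% of the round with six hamlets and 8/11 = 73% with twelve. The order of hamlets is not stated.

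**The case against.** An educational trial that declares itself open is not in error, and run lists and visit calendars are details that an article commonly leaves to a fuller document. That stands: silence on those two matters is no fault. The blinding sentence is different, because it is a stated decision and covers more people than it needs to.

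A reader might infer that assay run or season is confounded with arm. The documents do not support this. Neither run composition nor hamlet order is given. Section 2.3 admits only children with a baseline evaluation to the trial, which suggests that the baseline order was set before allocation. If that order were kept at six and twelve months, visit week would be unrelated to arm in expectation, and each hamlet's 12-month visit would fall in its own baseline season.

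A reader might also infer that the primary result is at risk from unmasked readers. Hemoglobin comes from a device, so this does not follow.

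Masking is weakest where judgement is greatest. Stool and urine are read within 24/48 h, and resident staff may know which hamlet was visited whatever the label says. This stands and limits the benefit.

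Finally, evaluation technicians also act as counsellors under Section 3.4. That is the larger assessor problem for diet, practice and reported-diarrhea outcomes, and laboratory masking does not touch it. It is a separate point and no reason to leave the laboratory unmasked.

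**Conclusion.** The point holds as a cheap improvement to a stated decision. Section 3.3 makes everyone unblinded when only families and counsellors need to be. The exposure that the text supports is unmasked visual reading of stool and urine for secondary infection outcomes, with a confirmation step not described as masked. Alignment of serum runs or visit weeks with arm is a possibility to exclude in advance, not something that the article says will happen.

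The size is modest and rests on assumptions: about 1 percentage point of false difference in an infection outcome for the shift and prevalence assumed above, and 7–14% of the mean in a serum marker only if runs followed arms. The benefit is mainly for secondary infection and micronutrient outcomes. For hemoglobin, only the visit calendar matters, and only if follow-up were worked arm by arm. It would be wrong to call the change free: labelling and run lists take work, and Section 3.1 describes the hamlets as geographically isolated.

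**What to change.** 1. Reword Section 3.3: families and counsellors are unmasked; laboratory readers, the supervisors doing the 25% confirmation and the data analyst are masked.
2. Label specimens by a study number that does not encode the hamlet, and withhold the hamlet-arm list from the laboratory. Results return to the treating staff by study number, so test-and-treat is unaffected.
3. Assay stored sera in runs that each contain all three arms, as nearly as possible in proportion to arm size.
4. Where travel allows, spread the arms across the 6- and 12-month calendar rather than working arm by arm. Strict sets of one hamlet per arm should not be required, because drawing in pairs can leave unequal arms (6/5/4 with fifteen hamlets).
5. State openly that masking of stool and urine readers is partial.

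The cost is some labelling and run-list work and possibly a less convenient travel order. No extra tests or staff are needed. The reading of specimens cannot be masked after the event, so the change belongs before the first follow-up.

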### 3.4. Training of Providers

Field and nursing technicians involved in the evaluation (baseline and follow up waves) will be assigned to the different intervention arms, being responsible for the counselling sessions (monitoring, encouraging and continuously promoting behavioral change), under the direction of a supervisor. Their previous training will be reinforced with theoretical and practical sessions on (1) the core aspects of the target disease and conditions (specifically, “What is the disease/condition”, “What are the signs and symptoms”, “What is causing them”, “What can mothers do to prevent them”), (2) counselling techniques (evaluating the emotional state of the caretaker and adapting counselling techniques to the emotional state), (3) household environment and risk behavior evaluation, according to the respective interventional arm they belong to. Within each intervention arm, they will perform one cycle of three-monthly visits to a group of households before then moving onto another group of families.

Following the first training stage, refresher sessions will occur before the follow up evaluation moments and before every domiciliary personalized counselling. At the beginning and at the end of each training stage, technicians will undertake a written evaluation test and a score will be generated. Additionally, 20% of all counselling sessions (per technician) will be subject to evaluation by a supervisor, who will similarly produce a counselling score for each trainee.

### 3.5. Training of Receivers

The receivers, i.e., the targets for the behavior change interventions, will be mothers and/or primary caretakers of the children studied. After the baseline assessment, the mothers in each intervention arms will be trained according to the respective “targets within the educational package” described in Table 1. The objective is to empower mothers with knowledge of basic principles regarding: (1) anemia and its nutrition-related etiologies and (2) anemia and its infections-related etiologies (in particular, what are the signs and symptoms? How did the child become at risk? How can mothers prevent this and what they should do whenever their children fall sick?) and to stimulate inadequate mother-to-child behavior changes. Technicians will document pre-and post-intervention alterations in the household environment and mother-to-child practices (according to the process indicators described in Table 2).

### 3.6. Recruitment and Promotion of Adherence

To relocate families, field technicians will perform a house-to-house invitation strategy, using Dande’s HDSS household identification system, reference points and family phone numbers. To increase adherence and promote participant retention, the hamlet coordinators and/or traditional authorities will be invited to be present at all phases of the study. Furthermore, incentive kits will be distributed to all children during the follow up moments, namely a nutritional kit (water and yogurt) and a WASH/Malaria kit (soap and lye).

### 3.7. Educational Package for Receivers

Families/caretakers allocated to the interventions are to receive six personalized counselling sessions at their homes and will be invited to participate in six community workshops for practice lessons. The overall treatment given in each arm, throughout the duration is described in Table 1.

Illustrative materials, adapted from UNICEF, will be used for these counselling sessions, as well as posters highlighting key health messages [60,61].

The practical cooking lessons within the nutrition study arm will aim at reinforcing the adoption of a diet with a Minimum Dietary Diversity and Minimum Meal Frequency and at increasing iron, folic acid, vitamin A- and B12-rich food ingestion [62]. Accordingly, after evaluating the ingredients available at the local market, aliments within the food groups of (1) grains, roots and tubers, (2) legumes and nuts, (3) dairy products, (4) flesh foods, (5) eggs, (6) vitamin A-rich fruits and vegetables, and (7) other fruits and vegetables will be identified, and easy, affordable and pleasant-to-the-palate recipes will be developed. Within those groups, food sources of heme-iron (red meat and poultry) and non-heme iron (specifically green leaves), will receive major attention [63,64,65,66,67]. Data collected at the qualitative study mentioned above, aiming at assessing the main feeding practices of infants and young children, will be used to assist this purpose. Classes will comprehend: (1) discussing the nutritional value of local foods, the effect of processing them on their nutrient value, (2) identifying the most common foodborne parasites, (3) demonstrating the fish-and-meat dishes to be used in the meals, (4) demonstrating combinations to be used at breakfast and lunch, (5) tasting and scoring recipes and (6) distributing illustrative recipe notebooks for practice.

The practical sessions within the WASH/malaria intervention arm will aim at preventing malaria, schistosomiasis and STH in children, particularly decreasing the transmission rate and consequently lowering their incidence and reinfection rates. Activities within the community groups will include: (1) identifying local points of possible STH contamination and children’s risk behaviors, (2) visiting target households to identify mosquito indoor resting and outdoor breeding sites, (3) constructing household washing-hand mechanisms, (4) correctly mounting of bed-nets and (5) running child hand-washing classes.

## 4. Data Collection

### Educational Interventions

Caretakers participating in the intervention arms will have a monitoring file (consisting of six structured questionnaires (one for each monthly visit), applied by the technician to document behavioral alterations at every counselling visit and to record attendance to the community group sessions. Those educational interventions will be intercalated with cross-sectional evaluations. Those moments will have the same design as the baseline assessment, occurring respectively six and twelve months after the beginning of the study.

Data on the primary and secondary outcomes, which will be collected only in the follow up moments, aim at evaluating the impact of interventions. Considering that interventions are expected to influence either health and behavioral aspects, impact indicators are expected to provide information on changes in their frequency, and potential associations. On the other hand, data on the process indicators, which will be collected throughout the study, aim at assisting the evaluation of the quality and success of intervention’s delivery process. Thus, data regarding the provision, utilization and coverage aspects of the delivery process are expected to facilitate attributing the changes in primary and secondary outcomes to the intervention, by demonstrating that the intervention was of sufficient magnitude and occurred in a temporal sequence. Specifically, (1) provision indicators are expected to inform about the quality of provider’s training and performance, and if the requirements for provider’s optimal performance was delivered to them; (2) utilization indicators are expected to inform about the quality of receiver’s sensibilization, their receptivity to interventional activities, acquired knowledge and alterations of inadequate behaviors toward children; and (3) coverage indicators aim at providing information regarding the quality of the interventional activities, such as the adherence to them.

